## Abstract

**Background:**

This paper presents the rationale and study protocol for a pragmatic controlled effectiveness trial of *Truce*, a prevention-based selective intervention targeting the significant mental health needs of young people who have a parent with cancer.

**Methods/Design:**

*Truce* is a seven week, facilitated, face-to-face group program. The design is a 2 groups (intervention vs control) x 3 (pre-treatment vs post-treatment vs 2 month follow-up) repeated measures. Allocation to groups will be dependent upon recruitment; when groups have sufficient numbers, they will be assigned to the intervention condition, but participants recruited without a viable group will be assigned to the wait-list control condition. Eligible participants are young people aged 14 to 22 years who have a parent diagnosed with cancer within the last 5 years. Wait-list controls are offered the opportunity to participate in the program once they have completed their follow-up questionnaires. The target sample size is 65 participants in each condition.

The primary hypothesis is that participants in the intervention will show significant reductions in distress and increases in psychological well-being relative to participants in the wait-list control group, and these effects will continue through two-month follow-up. Mixed-models analysis of variance will be used to measure differences between the two conditions. Secondary analyses will focus on variables which may relate to the effectiveness of the intervention: ACT-related concepts of experiential avoidance and mindfulness, family functioning, unmet needs and demographic variables. We will also assess program fidelity and satisfaction.

**Discussion:**

The development and evaluation of a manualised intervention for young people with a parent with cancer responds to a gap in the provision of empirically-based psychological support for this vulnerable group.

**Trial registration:**

Australian and New Zealand Clinical Trials Registry ACTRN12615000761561. Registered 22^nd^ July 2015.

## Background

### Supporting young people who have a parent with cancer

Each year, more than 21 000 Australian adolescents and young adults (aged 12–24 years) have a parent who is newly diagnosed with cancer (Patterson et al. 2014). For a young person, a parent’s cancer presents as a unique stressor with the threat of loss implicit in the diagnosis. Even when the prognosis is good, the young person may still be confronted by parental absences due to the need for hospitalisation, the ongoing impact of treatment side-effects upon the parent’s functioning, and disruption to normal family roles and routines, including shifts in responsibility for household duties and care of younger children onto the young people themselves (Romer et al. 2002; Welch et al. 1996; Maynard et al. 2013). Further, if the parent's cancer goes into remission, the young person still has to face the changes that the cancer brought, such as threat of recurrence and the possibility that the parent will no longer be able to act as carer (Osborn 2007). A young person’s experience of parental cancer is therefore likely to be disruptive and distressing across a number of psychosocial domains, with the added complication that the young person is already in a developmentally complex stage of life (Patton and Viner 2007).

Research on the psychological impact of having a parent with cancer has focused largely on young people’s internalising (e.g., anxiety and depression) and externalising (e.g., behavioural problems at school) symptoms as well as physical complaints (e.g., sleeping difficulties and headaches) and changes in cognitive function (e.g., maintaining concentration at school) (Visser et al. 2004). Research suggests that offspring of a parent with cancer exhibit relatively few externalising symptoms but that internalising symptoms are more common and elevated relative to community norms, especially among adolescents (as compared to young adults) (Visser et al. 2004; Osborn 2007). Furthermore, age and sex-related differences among offspring of parents with cancer generally indicate that adolescents and young adults experience more anxiety and depression than do pre-adolescent children, with the most elevated symptoms appearing in adolescent daughters of ill mothers (Compas et al. 1994; Romer et al. 2002; Osborn 2007; Welch et al. 1996; Visser et al. 2005).

The role of potential moderators of the psychological outcomes of young people who have a parent with cancer has also been examined. Key variables of interest have included: demographics (young person’s age and gender, parent’s gender, interaction between youth gender and parent gender); family make-up (parental marital status, presence/absence of siblings); disease variables (stage, prognosis, tumour type); treatment variables (no treatment, surgery, radiation, chemotherapy, combination of treatments); treatment outcomes/status (complications, side-effects, completion of treatment, recurrence of disease); time since diagnosis; prognosis; parent psychological functioning; family functioning (responsibilities, strain, roles, communication, cohesion, adaptability); and parenting (consistency, detachment) (Osborn 2007). Interestingly, disease and treatment variables do not appear to be associated with youth outcomes, nor do socio-demographic and parental mood variables, with the possible exception of maternal depression. The variables of greatest utility in predicting youth outcomes centre on family variables, especially those relating to family communication (McDonald et al. 2015; Osborn 2007).

Given the number of young people who have a parent with cancer, it is disheartening to note the scarcity of interventions specifically developed to assist this population (Lewis 2007; Romer et al. 2007). Recently, Niemela, Hakko and Rasanen (2010) conducted a systematic narrative review of interventions for offspring who have a parent with cancer and located only 11 structured child-centred interventions. They concluded that “..children are a forgotten group when families face a life-threatening parental illness.” (p.459). They found that interventions fell into two categories: structured family interventions and structured peer interventions. While results from family interventions were positive overall, the actual preventive effect of the interventions on children (for both the family and peer interventions) could not be evaluated due to the absence of follow-up. In general, the interventions lacked: a) methodological detail and theoretical underpinnings, b) reporting of results and use of valid outcome measures, c) substantial sample size, and d) control groups. All these factors prevent firm conclusions regarding the effectiveness of the interventions and highlight the pressing need for well-designed, controlled studies of interventions designed for the offspring of parents with cancer. The purpose of this paper is to provide researchers and practitioners with an outline of the development and content of a psychological intervention for young people who have a parent with cancer, and a rigorous study protocol designed specifically to evaluate the merits of an intervention.

### The Truce program

In consideration of the burden associated with a parent’s cancer diagnosis and the scarcity of programs available to support affected young people, there was a clear need for the development and evaluation of an intervention targeting the psychosocial and informational needs of this group. In response to this need, our research team^1^ developed *Truce*: a manualised 7-week, face-to-face group psychological intervention for young people who have a parent with cancer.

### Theoretical background – Acceptance and Commitment Therapy

*Truce* is part of an increasing movement to provide psychosocial support to people who present with risk, rather than waiting until a pathology is present, with the intention of reducing the likelihood of future psychosocial problems (Coie et al. 1993). This movement incorporates therapeutic paradigms that recognise client strengths and allow for growth (Kashdan and Ciarrochi 2013). Increasingly, the field of psychology has seen a shift from typical behavioural-only paradigms to cognitive - behavioural paradigms that emphasise changing the content of thoughts (Hollon and Beck 1994) to mindfulness-based therapies that emphasise changing one’s relationship with thoughts (e.g. Acceptance and Commitment Therapy, ACT). ACT teaches people to let go of destructive attempts to control feelings and to allow unhelpful thoughts to occur without “hooking to them” or believing them (Hayes et al. 1999). Overarching the ACT approach is the broader goal of increasing psychological flexibility, or the ability to adapt to shifting demands and maintain balance through the use of mental resources (Kashdan and Rottenberg 2010). In addition, ACT draws on the field of positive psychology, where the goal is to begin “… to catalyse a change in focus of psychology from preoccupation only with repairing the worst things in life to also building positive qualities” (Hayes et al. 1999, p. 5).

There are six core principles of ACT: *acceptance, defusion, being present, self as context, valued living and commitment to action* (Hayes et al. 1999; Bach and Moran 2008). *Acceptance* involves opening up in the service of values, and accepting painful internal experiences such as feelings and emotions instead of fighting them. *Defusion* refers to “unhooking” from thoughts; learning to observe them and not react to them, nor treat them as always true. *Being present* means consciously connecting to, and engaging with, the situation the person is currently in. *Self as context* refers to being aware of an internal, “observing self” distinct from the “thinking self”. *Valued living* involves identifying an individual’s personal values, that is, what is important to them. Finally, *commitment to action* refers to taking effective actions in a way that is consistent with one’s values (Hayes et al. 1999; Harris 2009).

### Previous ACT studies

Empirical evidence for the efficacy of ACT therapeutic approaches has previously been reviewed (Ruiz 2010). The review examined three types of study; namely, (i) correlational studies, (ii) experimental psychopathology and ACT component studies, and (iii) outcome studies. Results from the review highlighted a wide variety of conditions that have shown positive long-term outcomes from ACT treatment, including: depression, anxiety disorders, psychosis, chronic pain, and substance use. ACT therapies have demonstrated efficacy, producing large effect sizes that are typically maintained or increased at follow-up. Murrell and Scherbarth (2006) reported empirical support for ACT interventions across a variety of child and adolescent populations: adolescents at risk of dropping out of school (Moore et al. 2003), paediatric pain patients (McCracken et al. 2010), and adolescent girls either engaging in high-risk sexual behaviour (Metzler et al. 2000) or experiencing anorexia (Heffner et al. 2002). Further, research shows that for adolescents in school, ACT has good long-term effects at 2-year follow-up (Livheim 2004). Two randomised controlled trials for adolescents with depression provide further evidence of treatment efficacy (Hayes et al. 2011), and further recent evidence has been found for the effectiveness of ACT in helping adolescents with chronic pain (Gauntlett-Gilbert et al. 2012) and obsessive compulsive disorder (Armstrong et al. 2013). Finally, longitudinal research suggests that awareness and acceptance, both core concepts of ACT, are critical components of positive adolescent development (Ciarrochi et al. 2008, 2011; Marshall et al. 2015; Rowsell et al. 2014).

### The Truce facilitator manual, participant workbook and parent booklet

The working party involved in the development of *Truce* included consumer representatives who were young people impacted by parental cancer and psychologists with expertise in: developmental educational concerns, adolescent development, ACT, clinical work and young people impacted by cancer. A cancer nurse with clinical and research expertise and CanTeen staff with expertise in researching and working with young people and their families living with cancer, also contributed to the project.

The *Truce* program was developed to include all of the components of ACT (Hayes et al. 1999) and to gradually build and reinforce ACT skills and knowledge. It is a manualised, seven-session program (see Table 1) with the sixth session involving both the young person and their parent. In addition to the facilitator manual, a participant workbook and a parent’s booklet have been developed. The facilitator manual contains background information regarding the development and running of *Truce*, detailed content of each session, and all necessary worksheets and tools. The participant workbook contains review material for each session along with home practice activities which participants complete between sessions. Participants are given their workbooks in the first session and are not required to bring them to following sessions.

**Table 1 Tab1:** Content of the seven *Truce* sessions

Session	Content
*Session 1*. What happened to my ‘normal’ life!?	Welcome, establishing program engagement and group guidelines. Introduction to ACT and overview of the program. Psycho-education about the changes and accompanying psychosocial difficulties associated with having a parent with cancer. Opportunity to talk about how having a parent diagnosed with cancer has changed their life. Assisting the group to process how their experiences are similar and different between participants; normalising feelings, fears and concerns. Introduction to dealing with feelings, and grief and loss.
*Session 2*. Dealing with feelings	Developing understanding about the futility of trying to control unwanted feelings. Learning to have a different type of relationship with feelings; being willing to acknowledge them and allowing them to be there.
*Session 3*. Being Mindful	Introduction to the concept of mindfulness; learning to notice thoughts, feelings and physical body sensations; and understanding the importance of connecting with the present moment. Practising mindfulness in everyday life. Introduction and practice of the BOLD acronym: Breathing, Observing, Listening and Deciding.
*Session 4*. Sticky thoughts	Explores the concept of wanted and unwanted thoughts and the futility of trying to control thoughts. Introduction to the idea of the mind as a problem-finding and problem-solving machine. Introduction to the concept of sticky thoughts and learning to have a different, healthier relationship with them.
*Session 5*. Getting unstuck	Teaches strategies for getting unstuck from difficult thoughts to be able to refocus energy on better listening to what is important to us (values) and taking committed action towards those values.
*Session 6.* Values and Loving - Kindness	A combined session that brings the parent and child together to work on communication, values and loving - kindness. Increasing understanding of the importance of values to how we live our lives and that staying stuck to difficult thoughts prevents us from living well and heading in the direction we want to go in life. Learning to be unstuck to be free to listen to our values and decide on our actions. Practising loving-kindness toward ourselves and self-compassion; and using “wise view” to accomplish this.
*Session 7*. Taking action!	Identifying values and goals, and committing to take action to live in line with them by developing action plans. An opportunity to review and reflect on what has been learned in the *Truce* program over the seven sessions.

Given the aforementioned importance of family variables, the *Truce* program has been developed with consideration of Olson’s Circumplex Model, a family-focused framework (Olson 2000). Parents or caregivers who choose to participate are involved in the evaluation questionnaires and attend session six. A parent does not need to participate in the program in order for his or her child to participate. Likewise, the parent with cancer does not necessarily have to be the parent that attends session six.

The Parent Booklet will be given to parents prior to the commencement of the *Truce* program. The purpose of this booklet is to provide parents with information about the impact of parental cancer on young people and how they can support their child. Parents are encouraged to read the booklet prior to the commencement of their child’s participation in the *Truce* program. The booklet contains information on the *Truce* program and home practice activities, to be completed by the parent after he or she has attended the joint session. Specifically, the parent booklet contains information from research on the needs of young people who have a parent with cancer (Patterson et al. 2011) and information about what is helpful for young people who have a parent with cancer (Maynard et al. 2013). The ‘How you can help your child?’ section of the booklet has been structured on Olson’s Circumplex Model (Olson 2000).

## Methods/Design

### Study aims

The primary aim of the study is to evaluate the effectiveness of *Truce*, a 7-week ACT-based program for young people (aged 14 to 22 years) who have a parent diagnosed with cancer.

The primary outcome variables are distress and psychosocial well-being of intervention-group participants, relative to control-group participants, across the duration of the study (i.e., from pre-treatment through post-treatment and two - month follow-up assessment).

### Hypotheses

It is hypothesised that greater reductions in distress and improvements in psychosocial well-being will be observed in *Truce* program participants than in wait-list controls. Secondly, these effects will be maintained at two-month follow-up.

### Study design and setting

The study utilises a 2 (intervention vs control) x 3 (pre-treatment vs post-treatment vs two-month follow-up) repeated measures, within-between participants design. The two-month follow-up time was selected to provide a measure of the sustainability of the *Truce* program post-intervention, while minimising the waiting time before wait-list control participants commenced treatment.

The CONSORT guidelines for pragmatic trials (Zwarenstein et al. 2008) were used in the development of the study protocol, with the exception of randomisation of participants to intervention conditions. Pragmatic trials differ in emphasis from other randomised controlled trials in that they focus on examining effectiveness (i.e., they attempt to maximise the applicability of the trial to usual care settings) rather than efficacy (i.e., examining the impact of the intervention under ideal trial conditions) (Zwarenstein et al. 2008). Accordingly, we aimed to maintain methodological rigour within the constraints of working within realistic settings. Assignment of participants to the intervention or wait-list control condition will be determined by whether there are enough participants in an area to run a group (four to eight is the acceptable number for a group); where there are not enough participants, they will be assigned to the wait-list control condition. While not a true randomisation of participants, this approach lends external validity as it is similar to the circumstances around administering group therapy programs in the community.

The *Truce* program will be offered in a number of locations throughout Australia. The group meetings are to be hosted in private rooms in a range of locations such as CanTeen offices, Cancer Council offices and public spaces such as libraries. The program will be facilitated by both CanTeen staff and external facilitators, all of whom have been trained in ACT methods and who are experienced at working with young people. In addition to ensuring facilitators are appropriately trained and qualified, the *Truce* program is manualised (as described above) and all materials will be provided. Weekly briefing and debriefing sessions will be held with all facilitators to ensure the program is delivered according to the manual.

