### Sample size calculations

The sample will include a total of 130 young people who have a parent with cancer and, where possible, one parent of each young person. The number of required participants is based on sample size analyses assuming: 80 % power, alpha of 0.05 and a minimally important change in K10 scores of 4.9 (effect size of 0.5). According to these calculations, 65 participants are needed in each of the intervention conditions.

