### Data management and planned statistical analysis

Descriptive statistics will be used to report demographic information. Fidelity and satisfaction measures will also be summarised. Missing data will be managed using multiple imputation techniques. The impact of the treatment condition on the change in outcome variables will be assessed using mixed-models statistical analysis. Secondary analyses (such as testing for potential moderators and mediators) will be conducted using multiple regression statistical techniques.

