## Discussion

Young people who have a parent with cancer have many unmet needs (Compas et al. 1994; Patterson et al. 2011), but very little in the way of evidence-based programs that are designed to address these needs. Similarly, healthcare professionals who recognise the needs of these young people have few avenues for referral available to them. We hypothesise that *Truce* has the potential to provide considerable benefit to these young people, and that rigorous evaluation of the program will inspire healthcare professionals to refer to the program with confidence.

*Truce* has three clear strengths as a program for young people impacted by parental cancer. The first of these is that it is based on ACT, which has a considerable body of empirical evidence supporting its efficacy. ACT seems particularly suited to this client group for several reasons. ACT teaches young people to accept what can’t be changed, such as the threat of cancer, loss and the difficult feelings that arise. It also helps young people to engage in valued action, even in the presence of difficult feelings. Finally, ACT minimises the use of argument and complex problem solving and reasoning processes, which may particularly suit younger people whose abstract cognitive skills are still developing.

The second strength of the program is that it involves peer-to-peer interaction, which has been found to be an unmet need of young people who have a parent with cancer (Patterson et al. 2011). Participants are able to take part in a group where everyone is connected by a life circumstance that is often difficult to discuss on an everyday level with peers. Thirdly, it acknowledges the importance of a family systems approach.

The measures employed, as well as the use of a wait-list control group, will enable the impact of the program on the key outcome measures to be assessed. The longitudinal design will indicate whether post-intervention gains are maintained at follow-up. The design further allows us to identify factors that are likely to weaken or strengthen the effect of the intervention and the possible ACT processes behind the functioning of the intervention.

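### Truce is delivered in groups, but the article's sample size treats participants as independent and its described mixed model names no group level

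*Protocol article*

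**What the plan says.** **Delivery.** The abstract says that Truce "is a seven week, facilitated, face-to-face group program". Study design and setting gives the group size: "four to eight is the acceptable number for a group". Participants in an area that cannot fill a group go to the wait-list control, so controls have no delivery group during the comparison. The Discussion presents contact between group members as part of how the program works: "The second strength of the program is that it involves peer-to-peer interaction".

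**Analysis.** Study design and setting states: "The study utilises a 2 (intervention vs control) x 3 (pre-treatment vs post-treatment vs two-month follow-up) repeated measures, within-between participants design". The abstract states: "Mixed-models analysis of variance will be used to measure differences between the two conditions". Data management and planned statistical analysis states: "The impact of the treatment condition on the change in outcome variables will be assessed using mixed-models statistical analysis". None of these places lists random effects. None includes or excludes group, facilitator or area.

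**Sample size.** The section on sample size calculations assumes 80% power, alpha 0.05 and a "minimally important change in K10 scores of 4.9 (effect size of 0.5"), and concludes that "65 participants are needed in each of the intervention conditions". No ICC or design effect appears among the assumptions.

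**The concern.** This is a partially nested design. Members of one Truce group share facilitators, venue, sessions and each other's company for seven weeks, and they enter the intervention arm together. Their post-treatment scores are likely to be correlated. Controls have no such grouping.

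The article names two factors, condition between participants and time within participants, and the only unit it names is the participant. An analyst who follows that description literally would fit a model with participant as the only random effect. With a positive within-group ICC, that model understates the variance of the intervention-arm mean and therefore of the treatment contrast. If group is put into the model, inference is sound, but the 80% power behind the target of 65 no longer holds in general. Either the error rate or the power departs from what is stated.

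**Working it through.** **Inputs from the article.** Difference 4.9 K10 points at effect size 0.5, so the implied SD is 4.9/0.5 = 9.8. Alpha is 0.05; sidedness is not stated, and two-sided is used because one-sided gives 50 per arm and does not match. Power is 80%, with 65 per arm and group size m from 4 to 8.

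**Input assumed.** Within-group ICC of 0.01, 0.05 and 0.10. The article gives no value.

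**Step 1: reproduce the stated sample size.** For independent individuals, n per arm = 2(1.960 + 0.842)² / 0.5² = 62.8, rounded up to 63. The exact noncentral t calculation gives 64. At 65 per arm, power is 81.3% (normal) or 80.8% (t). The stated figure is therefore an individual-level figure with one or two participants to spare per arm.

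**Step 2: apply the design effect to one arm only.** DE = 1 + (m − 1) × ICC in the intervention arm and 1 in the control arm. With equal arms and equal total variance:

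- true SE / naive SE = √((DE + 1)/2)
- type I error with group omitted = 2[1 − Φ(1.96 / SE ratio)]
- power with clustering accounted for = Φ(0.5 / √((DE + 1)/65) − 1.96)
- n per arm for 80% power = (DE + 1)(1.960 + 0.842)² / 0.5²

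Example, m = 6 and ICC = 0.05: DE = 1.25. The SE ratio is √1.125 = 1.061, so type I error is 2[1 − Φ(1.848)] = 6.5%. Power is Φ(2.687 − 1.960) = 77%.

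| m | ICC | DE | SE ratio | Type I, group omitted | Simulated | Power, 65 per arm | n per arm for 80% |
|---|---|---|---|---|---|---|---|
| 4 | 0.01 | 1.03 | 1.007 | 5.2% | 5.1% | 81% | 64 |
| 4 | 0.05 | 1.15 | 1.037 | 5.9% | 5.7% | 79% | 68 |
| 4 | 0.10 | 1.30 | 1.072 | 6.8% | 6.7% | 76% | 73 |
| 6 | 0.01 | 1.05 | 1.012 | 5.3% | 5.3% | 80% | 65 |
| 6 | 0.05 | 1.25 | 1.061 | 6.5% | 6.2% | 77% | 71 |
| 6 | 0.10 | 1.50 | 1.118 | 8.0% | 8.0% | 72% | 79 |
| 8 | 0.01 | 1.07 | 1.017 | 5.4% | 5.4% | 80% | 65 |
| 8 | 0.05 | 1.35 | 1.084 | 7.1% | 7.0% | 75% | 74 |
| 8 | 0.10 | 1.70 | 1.162 | 9.2% | 9.2% | 69% | 85 |

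The simulated column comes from 40,000 runs per setting of a two-sample t-test at one time point that ignores group. With ICC zero it returns 5.0% within simulation error.

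**Step 3: number of groups.** 65/8 = 8.1 and 65/4 = 16.3, so about 8 to 16 groups. With so few, large-sample tests on a group effect are unreliable, and real power would be somewhat below the table.

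**The case against.** A reader might infer that the article plans a model that ignores clustering, and that type I error therefore exceeds 5%. The documents do not support that reading. The sentence on the 2 x 3 design describes the factorial layout, not the variance structure. A mixed model can carry a group effect, and the random effects are commonly left to a statistical analysis plan, which is not shown here. The individual-level sample size shows that no allowance was made for clustering when the trial was sized; it does not show that the analysis omits group.

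The size of any excess also depends on an ICC that the article does not give. At 0.01 it is trivial. The calculation covers a single post-baseline comparison, and adjustment for baseline could change both the relevant ICC and the SD. It says nothing about the moderator and mediator regressions, so the figures should not be carried to every secondary analysis. Because allocation turns on recruitment by area, controls may share areas too, and the calculation treats them as independent. Correlation between siblings is a further possibility, but the article does not say that siblings enrol.

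All of this stands and makes the type I figures conditional. It does not touch the sample size, whose inputs are listed in the article and leave clustering out. Nor does it remove the mismatch between a program delivered in groups and an analysis description that names only participants.

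**Conclusion.** The point holds in a conditional form. It is firm that the intervention arm is nested in groups of four to eight, that no group level is named in the analysis, and that 65 per condition is an independent-individuals figure. Two consequences follow over assumed ICCs of 0.01 to 0.10:

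- **If group is omitted and the ICC is positive,** type I error is about 5.2% to 9.2% against a nominal 5%.
- **If group is modelled,** power at 65 per arm runs from about 81% to 69%, and 64 to 85 per arm would be needed for 80%.

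Both rest on equal arms, equal total variance, independent controls, one post-baseline contrast and large-sample formulas. This is worth settling before analysis because it bears on the primary contrast and the remedy is cheap.

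**What to change.** 1. In Data management and planned statistical analysis, specify a partially nested linear mixed model: repeated measures within participant over the three assessments, plus a random Truce-group effect at the two post-baseline assessments in the intervention arm only, with controls as singletons.
2. Use Kenward-Roger or Satterthwaite degrees of freedom, because only about 8 to 16 groups are expected.
3. Carry group membership into the multiple imputation model, so that imputed values keep the within-group correlation.
4. In Sample size calculations, keep the 65 per condition but restate the power over a declared range of ICCs, for example from the table above. This does not call for more enrolment.

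The change is mainly one of wording. The data set must hold a group identifier for each intervention participant; the article describes an attendance checklist but does not say that it records group identity, so this should be confirmed. The price is slightly wider confidence intervals and a less favourable stated power.
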